## STUDY SAMPLE

### SAMPLE SIZE

The variable improvement in headache frequency has been chosen as a reference for calculating the sample size.

The calculation was made with the online program GRANMO 7.12 with the comparison menu between two independent means with a unilateral contrast and the following values: alpha risk 0.05; beta risk 0.20; to detect a difference equal to or greater than 3 units; a common standard deviation of 5 units; a ratio between the number of subjects between groups 1 and estimating a 15% loss to follow-up. The result is that 41 subjects per group are needed, as in this study there will be two groups, there are 82 subjects in total. Recruitment of this number of subjects is expected to be feasible.

The statistical data necessary to perform the calculation have been obtained from the study by Castien et al.(48) on the comparison of the application of manual therapy techniques versus usual medical treatment in patients with chronic tension-type headache, with an outpatient population in the Netherlands area.

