## DESCRIPTION OF THE INTERVENTION

Once the sample has been selected, an initial evaluation will be carried out, collecting data on the patient's clinical history using the anamnesis variables mentioned above. In addition, to identify more clinical characteristics of the sample of patients with tension-type headache, together with the clinical history, an assessment will be made of: the pressure pain threshold in the most relevant muscles of the cervical region by assessment with an algometer of pressure, cervical range of motion in the three planes of space using the CROM cervical range of motion measuring device and muscle length of the cervico-scapular muscles, the forward head position in sitting and standing by photometry, the resistance of the flexor musculature by means of the craniocervical flexion test (50) and the cross-sectional area of the deep cervical musculature by ultrasound.

Both groups will attend 3 sessions on alternate days for a week. Each of the sessions will consist of a pre-intervention assessment (intensity, frequency and location of the pain), an intervention (DF in the cranio-cervical region / Control) and a post-intervention assessment (intensity, frequency and location of the pain). In addition, a final complete assessment will be carried out 4 weeks after the last intervention. This assessment will be carried out throughout the study in the same time slot and will be preceded by some active warm-up exercises by the patient. The approximate time of each session will be 60 minutes.

Each treatment session of the Intervention Group will consist of a DF session in the cranio-cervical region, for 30 minutes, which will be directed mainly to the approach to the edges, insertions and insertional tendinous tissue of the following muscles: trapezius, paravertebral, angular scapulae, splenius capitis and neck, suboccipital, sternocleidomastoid, and temporal. The patient will be informed that the technique must be painless at all times and only a slight pricking sensation is allowed during hook traction (below 3 out of 10 on a VAS scale). The Control Group will receive the same assessments and will remain in the supine position for the same treatment time without receiving any intervention.

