#### DATA COLLECTION AND ANALYSIS

Those patients of the previously mentioned medical services, likely to participate in this study according to the corresponding medical specialist and who meet the inclusion and exclusion criteria will be referred to a physiotherapist to provide them with the information (oral and written) of the study. Those patients who decide to collaborate must sign the informed consent and will be assigned a correlative number. This same physiotherapist will be in charge of carrying out the initial, post-intervention and follow-up assessment, remaining blind to the assigned group. This assessment will include: Anamnesis, distribution of questionnaires, collection of data on the examination sheet related to pain, examination of the joint and muscular function of the cervical region, taking photographs to analyze posture and performing several ultrasounds of the cervical musculature.

A second physiotherapist, who will be the only one with access to the randomization list, will apply the diacutaneous fibrolysis technique to the patients assigned to the intervention group. It will also record the possible incidents or complications that may have occurred, such as bruises, skin reactions, etc.

As it is a manual technique, the physiotherapist cannot be blinded to the patient's condition, but allocation concealment is respected with this procedure.

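### Incident recording is assigned only to the unblinded treating physiotherapist, and no listed assessment asks either group about incidents, so comparable collection by arm and capture of events after session 3 are not assured

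*Protocol*

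**What the plan says.** All quotes here are from the protocol.

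- **Who records.** Data Collection and Analysis describes a second physiotherapist, the sole holder of the randomization list, who "will apply the diacutaneous fibrolysis technique to the patients assigned to the intervention group". The next sentence adds: "It will also record the possible incidents or complications that may have occurred, such as bruises, skin reactions, etc". No one else is given this task.
- **Who assesses.** The same section says of the first physiotherapist: "This same physiotherapist will be in charge of carrying out the initial, post-intervention and follow-up assessment, remaining blind to the assigned group". The content of that examination begins: "This assessment will include: Anamnesis, distribution of questionnaires, collection of data on the examination sheet related to pain". It continues with joint and muscle function, posture photographs and ultrasound.
- **When.** Under Description of the Intervention, "Both groups will attend 3 sessions on alternate days for a week", and "a final complete assessment will be carried out 4 weeks after the last intervention". The assessments around each session cover how strong the pain is, how often it occurs and where it is felt.
- **Control group.** The same section states: "The Control Group will receive the same assessments and will remain in the supine position for the same treatment time without receiving any intervention". It does not say who supervises these patients while they lie supine.
- **Outcome list.** The dependent-variables table runs from pain intensity to quality of life and has no row for incidents.

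**The concern.** The protocol expects that hook traction may cause bruising and skin reactions, and it plans to record them. Yet the one person named to do so delivers the technique and knows the allocation. What that person notices, asks about or counts as an incident may depend on knowing who was treated. No common method is fixed for the two groups, and no one is told to ask about incidents once the sessions are over.

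The protocol's own background makes these data worth collecting well. It reports only four indexed works on the technique, all on the extremities, and states that it has not been proven in trials of tension-type headache. An analysis plan cannot repair this later, because events that were never asked about cannot be recovered. At stake is how the trial's incident counts can be read: a low count could mean few events or few questions, and a difference between groups could reflect unequal questioning. The efficacy comparison is not at stake.

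**Working it through.** **1. The plan's own figure.** The protocol states no incident rate or other safety figure. The only number used below is the group size. Inputs from Sample Size: "unilateral contrast and the following values: alpha risk 0.05; beta risk 0.20", difference 3, standard deviation 5, ratio 1, loss 15%.

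- n per group = 2 × [5 × (1.645 + 0.842) / 3]² = 34.35
- allowing for loss: 34.35 / 0.85 = 40.4, rounded up to 41

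The stated 41 per group is reproduced. (Rounding to 35 first gives 35 / 0.85 = 41.2, so 42; the difference is immaterial here.)

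**2. Contacts set against incident questions.**

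| Contact | Who, as described | Incident item listed? |
|---|---|---|
| Initial assessment, both groups | First physiotherapist, blinded | No; the anamnesis variables contain none |
| Before and after each of 3 sessions, both groups | Post-intervention: first physiotherapist, blinded; pre-session assessor not separately named | No; pain items only |
| Treatment session, intervention group | Second physiotherapist, unblinded | Yes; incidents and complications recorded |
| Supine session, control group | Not stated | Not stated |
| 4-week assessment, both groups | First physiotherapist, blinded | No |

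The recording sentence gives no time window and names no arm. It neither confines recording to the treated group nor requires it in the control group. The one scheduled visit after session 3 is assigned to the physiotherapist who has no incident item to complete.

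**3. How much of follow-up comes after the last session.** Assume sessions on days 1, 3 and 5, with the final visit 28 days later on day 33.

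- by calendar days: 28 / 33 = 85%
- by elapsed days from the first session: 28 / 32 = 87.5%

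This is a share of time, not of risk. Bruising from traction would be expected near the sessions, so these percentages do not say what fraction of events would be missed.

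**4. What the counts could show at this sample size.**

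- Zero incidents in 41 treated patients gives a one-sided 95% upper limit of 1 − 0.05^(1/41) = 7.0%. With 35 completers it is 1 − 0.05^(1/35) = 8.2%.
- With both groups recorded at 41 each, two-sided power at 0.05 is about 86% for 30% against 5%, 75% for 20% against 2%, and 33% for 10% against 2%. These rates are assumptions; the protocol gives none.

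These limits come from the sample size and would be the same under the fix. They show that the by-arm table would be mainly descriptive, so its worth depends on both groups being asked in the same way.

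**The case against.** A reader might infer that the trial will have no control-group incident rate and that the recorder's contact with patients ends at session 3. The text supports neither statement. The recording sentence stands alone and is not limited to one arm. Control patients attend the same three sessions, someone must know their allocation to run them, and of the two people named only the second physiotherapist does. That person may well see control patients too. No cut-off for recording is set, and a late problem could come up in the 4-week anamnesis or examination, or be reported back. This stands, so the point is that collection is not specified, not that it is known to be absent.

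A reader might also infer that a flare of headache could not be told apart from background. It can. Pain intensity, frequency and location are assessed in both groups around every session, with a complete assessment at 4 weeks and a blinded assessor. Pressure pain threshold and muscle tenderness are dependent variables too, which partly covers persistent soreness. This also stands, and headache worsening is left out of the gap.

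It can further be said that supine controls are not touched by hooks, so a comparator adds little for local bruising; that no objective concerns safety; and that giving incidents to the unblinded therapist protects the assessor's blinding. Each has some force and limits how serious the point is. None supplies a fixed way of asking, a question after session 3, or a check on recording by the provider alone. No proportion of missed events can be given either, since any such figure would rest on an assumed bruise rate and timing.

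**Conclusion.** The point holds as a gap in specification. The protocol makes the unblinded treating physiotherapist the only named recorder of incidents, and none of its listed assessments asks either group about them, including at 4 weeks. Comparable collection in the control group and capture of events after session 3 are not assured, and recording by the provider alone is open to ascertainment bias.

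The gap covers bruising, skin reactions, short-lived soreness and other incidents. On the assumed schedule of days 1, 3 and 5 it extends over 85% to 87.5% of follow-up time, depending on how days are counted; the share of events affected is unknown. The sample size and the efficacy comparison do not change. This is an inexpensive improvement that should be made, not a defect that undermines the trial.

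**What to change.** - **Description of the Intervention, and Data Collection and Analysis:** have patients in both groups complete the same short event form before sessions 2 and 3 and at the 4-week visit. It covers bruising or skin marks, soreness and anything else, each with onset and duration. Patients complete it themselves and seal it, so the blinded assessor does not see it.
- **Data Collection and Analysis:** state that the second physiotherapist keeps the session incident log for both groups.
- **Reporting:** state that incidents are reported by arm for all randomised patients. This matters because the eligibility criteria require attendance at every session and exclude those who do not complete them, so a patient who stops because of a reaction could otherwise drop out of the count.

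The cost is a one-page form, a few minutes per visit and one descriptive table, with no extra visits or staff. The real downside is that asking about skin marks shortly before a blinded assessment could prompt a patient to reveal the allocation. The form should therefore be handed out and collected by someone other than the assessor, and patients reminded not to discuss it.

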#### STATISTIC ANALYSIS

The statistical study will be carried out with the SPSS version 22.0 for Mac program. The confidence level established for the analysis of the results will be 95%. The person who will analyze the results will be blinded to the interventions assigned to each subject.

To achieve the objectives of the study, a descriptive study, a comparative study, a correlational and regression study of the collected data will be carried out.

For the descriptive analysis of the quantitative variables, the central tendency indices (mean and median) and the dispersion indices (standard deviation and the minimum and maximum values) will be used. For qualitative variables, a study of frequencies will be carried out to find out the absolute and relative frequencies, and the valid and cumulative percentages. In some cases, the mode central tendency measure will be extracted.

Prior to carrying out the comparative study between both groups, a study will be carried out to determine the normality and homoscedasticity of the study's scale variables and thus be able to use the corresponding statistical operations.

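### The between-group test is left to normality and variance pre-tests, so the estimand is not fixed, and no baseline-adjusted comparison is stated although baseline headache frequency is collected

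*Protocol*

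**What the plan says.** **How the test is chosen.** STATISTIC ANALYSIS places a study of normality and homoscedasticity first: "Prior to carrying out the comparative study between both groups". Its stated purpose concerns the "scale variables and thus be able to use the corresponding statistical operations". No test, model, estimand or covariate is named. The section also announces correlational and regression work, without giving an outcome or covariates.

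**What the trial is sized on.** SAMPLE SIZE says: "The variable improvement in headache frequency has been chosen as a reference for calculating the sample size". For the method it cites "the comparison menu between two independent means with a unilateral contrast". Alpha is set at 0.05 and power at 80%, and the target difference is 3. The spread is entered as "a common standard deviation of 5 units". With equal arms and 15% loss, this gives 41 per group and 82 in total. It contains no covariate. It does not say whether the SD is that of the follow-up value or of the change.

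**What is measured.** The first table under STUDY VARIABLES lists headache frequency, in days, among the history items. DESCRIPTION OF THE INTERVENTION takes these at the initial evaluation and adds a complete assessment 4 weeks after the last session. The DEPENDENT VARIABLES table lists frequency again, from a registration sheet.

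**The concern.** The two sections do not join up. The sizing presupposes a difference in means. The analysis rule allows the final comparison to be something else, depending on how the pre-tests fall. On the rank branch the trial could report a p-value with no estimate in days, which is the scale on which 3 units was judged worth detecting. Two trials drawn from the same population could then report different quantities.

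Baseline adjustment is a separate matter. Eligibility admits both episodic and chronic tension-type headache. The introduction separates these subtypes by frequency and duration, so baseline frequency should vary widely. RANDOMIZATION describes no stratification, so chance imbalance between arms is possible. Using the baseline value as a covariate would remove that imbalance from the estimate and shrink the residual variance. The protocol does not say that this will be done.

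**Working it through.** **1. The plan's own figure.** Inputs from SAMPLE SIZE: difference 3, SD 5, one-sided alpha 0.05, power 0.80, ratio 1:1, loss 15%.

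n per arm = 2 × [5 × (1.645 + 0.842) / 3]² = 34.35, and 34.35 / 0.85 = 40.41, which rounds up to 41. The stated figure reproduces. Rounding to 35 before inflating gives 35 / 0.85 = 41.2, so 42, a trivial difference. Expected completers are 41 × 0.85 = 34.85, taken as 35 per arm.

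**2. Unadjusted power at 35 per arm.** Noncentrality = 3 / (5 × √(2/35)) = 2.51. The noncentral t distribution gives 80.0% one-sided (the protocol's basis) and 69.7% two-sided.

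**3. Power with the baseline value as covariate.** Let baseline and follow-up have equal variance σ² and correlation r. Neither r nor equality of variances is in the protocol; both are assumptions.

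- Variance of change: 2σ²(1 − r). ANCOVA residual variance: σ²(1 − r²). Their ratio is (1 + r)/2.
- If 5 is the SD of change, residual SD = 5 × √((1 + r)/2).
- If 5 is the SD of the follow-up value, residual SD = 5 × √(1 − r²).

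| r (assumed) | Meaning of SD 5 | Residual SD | Power, one-sided | Power, two-sided |
|---|---|---|---|---|
| unadjusted | either | 5.00 | 80.0% | 69.7% |
| 0.3 | change | 4.03 | 92.5% | 86.6% |
| 0.5 | change | 4.33 | 89.0% | 81.5% |
| 0.7 | change | 4.61 | 85.3% | 76.5% |
| 0.3 | follow-up | 4.77 | 83.1% | 73.7% |
| 0.5 | follow-up | 4.33 | 89.0% | 81.5% |
| 0.7 | follow-up | 3.57 | 96.7% | 93.4% |

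The covariate costs one degree of freedom (67 instead of 68), which moves these figures by less than 0.1 percentage point.

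**4. How often the pre-test would switch the estimand.** The protocol names no normality test. As an assumption, take Shapiro-Wilk at 5% in each arm of 35, with a rank test used if either arm fails. Exactly normal data go to the rank test in about one trial in ten (1 − 0.95² = 9.75%). In simulation, mildly skewed data (gamma, shape 8) go there about half the time, and clearly skewed data (gamma, shape 2) in about 97% of trials.

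**5. Whether the pre-test harms error rates.** Simulation with 35 per arm and 8,000 runs per setting; Shapiro-Wilk and Levene chose between t, Welch and Mann-Whitney; one-sided 5%. Type I error was 0.051 (normal) and 0.048 (skewed). Power was 0.798 against 0.798 for the plain t-test (normal), and 0.921 against 0.789 (skewed, pure shift). A two-sided repeat over four distributions, identical in both arms, gave type I error from 0.045 to 0.052. There is no sign of harm in these settings.

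**The case against.** Several objections have force.

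- **Silence is not exclusion.** No test or covariate is named, regression is mentioned, and an SAP not shown may supply the model. This stands as regards adjustment: it is unstated, not ruled out. It does not dispose of the pre-test rule, which is written into the protocol and would have to be withdrawn.
- **Improvement probably already uses baseline.** This largely stands. If it means change from baseline, the fair criticism is a change score where ANCOVA would do better. The gain over a change score shrinks as r rises: at r = 0.9, two-sided power is only about 72% against 69.7%.
- **The trial meets its target without adjustment.** On the protocol's one-sided basis, 80.0% is what was planned. This stands. The lower two-sided starting point belongs to the separate question of sidedness.
- **The baseline and follow-up tools may differ.** Frequency comes from the history at baseline and appears against a registration sheet as an outcome. If these are different instruments, r could be low, and under the follow-up-SD reading the gain would be small (83.1% at r = 0.3).
- **Headache subtype is not a listed variable.** It appears only in the eligibility diagnosis, and it overlaps with baseline frequency. It cannot be assumed available as a covariate.

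A reader might infer that choosing the test from the data distorts the type I error here, or that the pre-tests themselves lose power. Nothing in the protocol shows either, and the simulations point the other way. Nor should a reader infer that the sample size is wrong: it reproduces.

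**Conclusion.** The point holds as an improvement to the plan, not as an error in a stated figure. It has two parts.

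First, the rule in STATISTIC ANALYSIS leaves the choice between a mean difference and a rank comparison to the trial's own data, so the reported quantity may not match the difference on which the trial was sized. This needs no assumption beyond the text; how often a switch would occur depends on the pre-test and the data distribution.

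Second, no baseline-adjusted comparison is stated although the baseline value will be in hand. One-sided, adjustment adds about 5 to 12 percentage points of power if SD 5 is that of change, and about 3 to 17 points if it is that of the follow-up value. These ranges rest on r between 0.3 and 0.7 and on equal baseline and follow-up variances. The direction of the gain is the same under both readings of the SD; its size is uncertain.

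**What to change.** Replace the pre-test rule with one method named in advance:

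- **Primary model:** ANCOVA of headache frequency at the 4-week assessment on group and baseline frequency. Report the adjusted difference in days with a 95% interval and heteroscedasticity-robust standard errors.
- **Normality and variance checks:** diagnostics only, with no bearing on which result is primary.
- **Sensitivity analysis:** a rank-based or count model, named beforehand.
- **Other quantitative outcomes measured at baseline:** the same form of model.
- **Headache subtype:** add it as a covariate only if it is recorded from the eligibility diagnosis.
- **Measurement and SD:** record frequency in the same way and over the same period at baseline and follow-up, and say whether the SD of 5 refers to change or to the follow-up value.

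The cost is one paragraph of analysis text and one degree of freedom. The primary model needs no new variable and no extra participants.

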## WORKPLAN

### STAGES OF DEVELOPMENT

1. Complete the literature search: January 2015
2. Analysis of the bibliography and drafting of the project: April 2015
3. Submission to the Ethics Committee: June 2015
4. Recruitment of subjects: September 2015 - September 2016
5. Data analysis: November 2016
6. Writing of the results: February 2017
7. Presentation of the thesis: Spring 2017

